### Specific objectives and hypotheses

The following randomized controlled trial (RCT) protocol was designed to evaluate the effect of the COGNI-MACHINE computational thinking training program on the executive functions of fifth-grade children aged 9 to 11 years. This RCT has established the following working hypothesis:

There are significant differences in the evolution of executive functions and other cognitive processes, such as metacognition and attention, in fifth-grade children who receive training in computational thinking compared to those children who receive a conventional computer training program.

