**Fig. 1 fig0001:**
[figure not shown]
Layout of the experimental design. *Note:* RG1: Experimental group; RG2: Control group; On: Measure; X: Intervention.

For the intra-subject analysis, each group will be evaluated before starting the intervention (T1) and after the intervention (T2). Three months after the end of the intervention, a third follow-up measure (T3) will be applied to the experimental group to recognize the permanence of the effect over time. Once the post-test phase is over, the control group will receive the same training in computational thinking. For the intersubject analysis, the study will include an active control group in treatment as usual (Treatment-As-Usual - TAU), which consists of receiving the usual treatment in parallel to the experimental group and for the same time as the experimental group [[67], [68]].

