### Statistical analysis plan

A hypothesis test will be conducted through Mixed Repeated Measures Analysis of Variance (ANOVA MR) with Bonferroni corrections to look at the differences between groups, in which the pre-test, post-test, and follow-up measures will be the factor of repeated measures. (Within-subject) and the difference between the experimental and control groups as the subject factor. The effect size will be measured with partial eta squared. The assumptions of this type of analysis assume a continuous metric-dependent variable with approximately normal distribution and with homoscedasticity in each of the groups.

A multivariate linear regression analysis will also be performed to assess the correlations between cognitive measures and computational thinking. And logistic regressions to analyze binary variables to evaluate the association between the covariates and the results.

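### The hypothesis is a between-arm difference in change, but the plan does not say which effect of its three-level ANOVA decides it; read literally, it is the weak group factor

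*Protocol article*

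**What the plan says.** Under Specific objectives and hypotheses, the working hypothesis reads "There are significant differences in the evolution of executive functions and other cognitive processes" between children given the training and children given conventional computer classes. That is a statement about change over time compared across arms.

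The Statistical analysis plan section specifies a Bonferroni-corrected mixed repeated-measures ANOVA "to look at the differences between groups, in which the pre-test, post-test, and follow-up measures will be the factor of repeated measures". The three time points thus form the within-subject factor, and "the difference between the experimental and control groups as the subject factor" gives the between-subject factor. Effect size is partial eta squared, but the effect it belongs to is not named. No passage mentions an interaction, a difference in change or a comparison adjusted for the pre-test score. Covariate measures lists sociodemographic and participant-specific factors and does not name the baseline score.

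The text under Fig. 1 in Protocol design divides the evaluation into an intra-subject part (T1 and T2 in each group) and an inter-subject part (group against group). It also says that "a third follow-up measure (T3) will be applied to the experimental group" and that controls receive the training once the post-test phase is over. The Control group section repeats that exchange of programmes after week 12. Table 2 nevertheless counts three measures for two groups.

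**The concern.** A two-factor mixed ANOVA returns three tests: group, time, and group by time. Only the last bears on a hypothesis about different evolution. The stated purpose of the test fits the group effect more naturally. That effect compares the arms on the average of all time points, including a pre-test taken before any training, so a real effect is diluted.

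The time factor adds a second difficulty. If T3 exists only for the experimental arm, the three-level factor cannot be filled for controls. If controls were measured at T3, they would by then have started or completed the training. In neither case does the third level compare trained with untrained children.

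At stake is whether the trial's main question is answered by a well-powered, clearly identified contrast, or by whichever of several effects is later taken as the answer.

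**Working it through.** **Inputs from the document (Table 2):** 2 groups, 3 measures, alpha 0.05, power 0.95, effect size 0.25 to 0.5, 22 per group, N = 44.

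**Assumptions, not in the document:** the effect size is Cohen's f (the metric is not stated); equal correlation rho between measures; sphericity; SD of 1 at each time; two-sided 5% tests; children independent, to isolate the choice of effect.

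**1. Reproducing the plan's 44.** For the interaction, lambda = f²·N·m/(1 − rho), with df 2 and 2(N − 2). At f = 0.25, m = 3, rho = 0.5:
- N = 44: lambda = 0.0625 × 44 × 3 / 0.5 = 16.5, df 2 and 84, power 0.956.
- N = 42: lambda = 15.75, df 2 and 80, power 0.946.

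So 44 is the smallest even N that reaches 0.95. With two groups the time main effect has the same lambda and df, so the figure does not show which of the two was meant.

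**2. The group factor at the same inputs.** lambda = f²·N·m/(1 + (m − 1)·rho) = 8.25 / 2 = 4.125, df 1 and 42, power 0.51. Reaching 0.95 takes N = 142 (lambda 13.31, power 0.952). Power at N = 44 for other correlations:

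| rho | Interaction | Group factor |
|---|---|---|
| 0.3 | 0.865 | 0.60 |
| 0.5 | 0.956 | 0.51 |
| 0.7 | 0.998 | 0.44 |

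**3. The same training effect put through each test.** With three measures, one f does not describe the same pattern of means for both effects, so a common scale is fairer. Take a true effect of 0.5 SD at T2 with 22 per arm. The noncentrality is d·√(22/2), with 42 df (41 for the adjusted test).

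| Test | d | d at rho 0.5 / 0.8 | Power at rho 0.5 / 0.8 |
|---|---|---|---|
| T1-to-T2 change contrast | 0.5/√(2(1 − rho)) | 0.500 / 0.791 | 0.37 / 0.73 |
| Group factor, T1 and T2 | 0.25/√((1 + rho)/2) | 0.289 / 0.264 | 0.15 / 0.14 |
| Group factor, three measures, effect at T2 and T3 | 0.333/√((1 + 2·rho)/3) | 0.408 / 0.358 | 0.26 / 0.21 |
| T2 adjusted for T1 | 0.5/√(1 − rho²) | 0.577 / 0.833 | 0.46 / 0.77 |

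The third row is generous to the group factor: it supposes that controls stay untrained through T3.

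**4. Why step 1 gives 0.956 and step 3 only 0.37 at rho 0.5.** The effects differ in size. With two measures, f = 0.25 on the interaction means ±0.25 SD in each of the four cells, a difference in change of 4 × 0.25 = 1.0 SD. Check: lambda = 0.0625 × 44 × 2 / 0.5 = 11 = (1.0/√(2 × 0.5))² × 11. Step 3 uses half that effect. At f = 0.25 and rho = 0.5 a two-measure interaction has power 0.90 at N = 44 and needs N = 54 for 0.95.

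**The case against.** The strongest reply is that this is only missing wording. A mixed ANOVA with these two factors yields the group-by-time interaction by construction. It is introduced as the hypothesis test, and the only hypothesis stated concerns evolution. N = 44 agrees with sizing on the interaction and not, at f = 0.25, with the group effect. Naming the deciding term could be left to a fuller plan.

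Much of this stands. The model can answer the question, and nothing shows that the authors intend the group main effect. At the upper end of Table 2 (f = 0.5) even the group factor has power 0.952 to 0.993 at N = 44 for rho 0.7 to 0.3. What remains is that the printed purpose of the test does not match the hypothesis, and that the three-level factor conflicts with the design text on who is measured at T3 and when controls are trained. Those are conflicts in the text, not omitted detail.

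A reader might go further and infer that a baseline gap, or a significant gain in the trained arm alone, would produce false claims of efficacy at a raised rate. The documents do not support that. With independent children, a chance baseline gap is already inside the group test's 5% error rate; a higher rate appears only if a fixed gap is assumed. No passage bases efficacy on significance in one arm and not the other: the intra-subject text mainly says when each group is measured. Systematic gaps between intact classes are a clustering problem, which naming the interaction would not cure.

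**Conclusion.** The point holds as a mismatch between the hypothesis and the stated test, in a model that can answer the question. If the group factor were taken as decisive, power would be 0.51 instead of 0.956 at f = 0.25, rho = 0.5 and N = 44. For a 0.5 SD effect at T2 with 22 per arm it would be 0.14 to 0.15 instead of 0.37 to 0.73 for the change contrast. If the three-level interaction were taken, its third level would not compare trained with untrained children, so T1 to T2 is the only clean contrast between the arms.

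These figures rest on assumed correlations, on reading Table 2's effect size as f, and on treating children as independent although four classes are randomised. The true power of every test here also depends on clustering, which this point leaves aside. The 44 is not shown to be wrong for a three-measure interaction that ignores clustering. The change should be made, but it does not call for a different model family.

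**What to change.** In the Statistical analysis plan section:

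- Name one deciding test for each primary measure: the between-arm difference at T2 adjusted for T1.
- The T1-to-T2 group-by-time contrast is a close alternative but not an equivalent one, so choose one in advance. As an illustration, with a stable 0.3 SD baseline gap and no effect, the change contrast is 0, while the adjusted difference is 0.3(1 − rho), that is 0.15 to 0.06 SD for rho 0.5 to 0.8.
- State that the group and time main effects, the intra-subject T1-T2 comparisons and the experimental-arm T3 are descriptive.
- Reconcile the three-measure factor, here and in Table 2, with the Protocol design text on T3 and on when controls are trained.

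The cost is one or two sentences and no new data. Within-group and main-effect p-values can then no longer be used to support efficacy. The change does not deal with clustering by class, which needs separate treatment.

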### Inclusion and exclusion criteria

This study will include children in fifth grade of primary school between 9 and 11 years old. Table 1 contains the criteria for including data from children in the controlled trial.

**Table 1 tbl0001:** Inclusion and exclusion criteria.

Inclusion criteria	Exclusion criteria
1. Children of both sexes.	1. Children with uncorrected sensory impairment.
2. Children who at the time of the beginning the study are between 9 and 11 years old.	2. Children with a psychiatric diagnosis.
3. Children enrolled in fifth grade of primary school in an educational institution of Ibagué, Colombia.	3. Children who exceed the age range at the beginning of the pre-test.
4. Children with typical cognitive development.	4. Children with previous experience in computational thinking, coding or programming training.
5. Children who have participated in 70% of the intervention.	5. Children who have joined the educational institution after the application of the pretest.

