#### Covariate measures

Sociodemographic and participant-specific factors from both groups will be measured and treated as covariates to describe the population and assess the effectiveness of the intervention. The socioeconomic level (SES) will be estimated with the sociodemographic stratum registry of the National Planning Department (DANE) [86], and other socioeconomic variables, such as parental education, access to technological means, among others, will be evaluated with the Sociodemographic Characterization Questionnaire [87].

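### The mixed ANOVA uses the pre-test only as a repeated level; making T2 adjusted for the pre-test the primary contrast would usually be more precise, and the two sections on covariates need reconciling

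*Protocol article*

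**What the plan says.** The Statistical analysis plan section names the method: "A hypothesis test will be conducted through Mixed Repeated Measures Analysis of Variance (ANOVA MR) with Bonferroni corrections", "in which the pre-test, post-test, and follow-up measures will be the factor of repeated measures", "and the difference between the experimental and control groups as the subject factor". The pre-test thus enters as one of the repeated outcomes. Group is the only between-subject term named.

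On covariates, two sections differ. Covariate measures says that sociodemographic and participant factors "will be measured and treated as covariates to describe the population and assess the effectiveness of the intervention". The Statistical analysis plan names none in the ANOVA and gives them one place: "logistic regressions to analyze binary variables to evaluate the association between the covariates and the results". The primary measures in Table 4 are counts, spans and times, so logistic models for binary variables do not reach them as listed.

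Two design facts bear on the choice of contrast:
- Every analysed child should have a pre-test. Table 1 excludes "Children who have joined the educational institution after the application of the pretest", and the text under Fig. 1 has both groups assessed at T1 and T2.
- The same text says that "a third follow-up measure (T3) will be applied to the experimental group", and the controls receive the training once the post-test is over. T2 is therefore the only time after baseline that is measured in both arms.

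**The concern.** When the pre-test is a level of the repeated factor, the T1-to-T2 part of group by time equals the difference between arms in mean change. That subtracts the whole baseline score from each child's post-test. Unless the pre-post correlation is 1, subtracting the whole score brings in more baseline noise than regressing on it does. For independent children, T2 adjusted for T1 is then the more precise estimate of the same effect.

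Precision matters here: the minimum sample is 44 children in four classes. The data needed for the better contrast are already collected. The plan also says that covariates will help to judge effectiveness without giving them a model in which they could do so for the primary scores.

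**Working it through.** **Inputs.** From Table 2: effect size 0.25 to 0.5 (metric not named; read here as Cohen's f), alpha 0.05, power 0.95, 2 groups, 3 measures, 22 per group. From Recruitment and Assignment: four classes and about 100 children expected. The article gives no pre-post correlation, intraclass correlation (ICC) or difference in SD units, so these are assumed below.

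**1. The plan's own figure.** For the group-by-time interaction, λ = f²·N·m/(1−ρ), with df (k−1)(m−1) and (N−k)(m−1). With f = 0.25, N = 44, m = 3, k = 2, and ρ = 0.5 and sphericity assumed, λ = 0.0625 × 44 × 3 / 0.5 = 16.5 on 2 and 84 df. Power is 0.956, and 44 is the smallest even total that reaches 0.95. The arm main effect would instead need 142 (f = 0.25) or 38 (f = 0.5). The stated 44 therefore fits the interaction and not the main effect.

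**2. Variance of the T2 contrast, independent children, outcome SD 1.**
- Change score: 2(1−ρ).
- T2 adjusted for T1: 1−ρ².
- Ratio: (1−ρ²)/[2(1−ρ)] = (1+ρ)/2.

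**3. Power at 22 per arm, assumed difference 0.5 SD, clustering ignored.** Noncentrality = 0.5/√(variance × 2/22), with 42 df for change and 41 for adjusted.

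| Assumed ρ | Change variance | Adjusted variance | Ratio | Power, change | Power, adjusted |
|---|---|---|---|---|---|
| 0.3 | 1.40 | 0.91 | 0.65 | 0.28 | 0.40 |
| 0.5 | 1.00 | 0.75 | 0.75 | 0.37 | 0.46 |
| 0.7 | 0.60 | 0.51 | 0.85 | 0.55 | 0.62 |
| 0.9 | 0.20 | 0.19 | 0.95 | 0.95 | 0.96 |

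At an assumed 1 SD the pairs are 0.78 v 0.92, 0.90 v 0.96 and 0.987 v 0.995 at ρ = 0.3, 0.5 and 0.7.

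**4. Cost in degrees of freedom.** One child-level baseline term moves the critical t from 2.018 (42 df) to 2.020 (41 df). Terms with no prognostic value inflate variance by roughly 41/37 = 1.11 for four and 41/33 = 1.24 for eight. Inference at class level has 2 df (critical t 4.30). A class-level covariate would leave 1 df (critical t 12.71).

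**5. Does the ratio survive four classes?** Take ICC 0.10 and total pre-post correlation 0.5, both assumed, and adjust with the within-class slope b, treated as known. With n children per class, the variance of a class mean is V = 0.10 + 0.90/n, and C is the T1–T2 covariance of class means. The contrasts are proportional to 2(V−C) for change and (1+b²)V − 2bC for adjusted.
- Class-level correlation 0.5: b = 0.5 and C = 0.5V, so the ratio is 0.75V/V = 0.75 at any class size.
- Class-level correlation 0.95: between-class covariance 0.095, within-class covariance 0.50 − 0.095 = 0.405, b = 0.405/0.90 = 0.45.
  - 11 per class (44/4): V = 0.1818, C = 0.095 + 0.405/11 = 0.1318. Change 0.1000, adjusted 0.2186 − 0.1186 = 0.1000. Ratio 1.00.
  - 25 per class (100/4): V = 0.1360, C = 0.095 + 0.405/25 = 0.1112. Change 0.0496, adjusted 0.1635 − 0.1001 = 0.0635. Ratio 1.28.

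The gain holds in full when classes behave over time as children do. It disappears or reverses when class means are far more stable than individual scores.

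**The case against.** The strongest defence is that the planned test fits the stated hypothesis. Specific objectives and hypotheses speaks of differences in how executive functions evolve, which is what group by time tests. Several stronger readings are tempting, and the article does not support them.

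- *Baseline is ignored.* It is not. The interaction already removes each child's baseline level; the shortfall is one of efficiency.
- *The test is the arm main effect, diluted by a pre-test that cannot show an effect.* That test would have power of about 0.46 at 1 SD with two measures and ρ = 0.5. But the section does not name the tested term, and both the hypothesis and the reproduced 44 point to the interaction.
- *Adjustment is always better and free.* Step 5 shows otherwise for four classes, and step 4 shows that a long covariate list has a price.
- *Change scores are biased by baseline imbalance.* Under random allocation, chance imbalance adds variance and not systematic bias. Adjusting for the child's score need not remove a class-level difference.
- *The change would bring power above 0.9.* The figures that suggest this assume 1 SD and independent children, whereas an analysis that respects class has about 2 df.

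It is also fair to say that a condensed article may leave the covariate list to a fuller analysis plan. That limits the weight of the covariate point. What remains is that the article fixes a specific primary model and assigns the covariates to a place that does not match its own statement of their purpose.

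**Conclusion.** The point holds as an efficiency improvement. The stated model uses the pre-test as an outcome level only. Conditioning T2 on it would cut the variance of the arm contrast by 35%, 25%, 15% or 5% at assumed correlations of 0.3, 0.5, 0.7 or 0.9, if children were independent. At 0.5 SD and 22 per arm, power stays low on either analysis unless the correlation is very high. With four classes the gain depends on how stable class means are over time, which the article does not tell us; it could be nil or negative.

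Nothing here invalidates the planned interaction test, and the change does not make up for having only four classes. Separately, Covariate measures and the Statistical analysis plan do not agree on where the covariates enter, and this needs reconciling.

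**What to change.** - Make the arm difference at T2 the primary contrast for each primary outcome, adjusted for the child's T1 score on the same test, with class accounted for and small-sample degrees of freedom.
- Report the adjusted mean difference with a 95% confidence interval beside partial eta squared.
- Keep the T1-to-T2 group-by-time result as a prespecified sensitivity analysis. It also guards against the case in which class means are very stable.
- Limit any further adjustment to one or two prespecified child-level covariates, with none at class level.
- Reconcile Covariate measures with the Statistical analysis plan by naming the model in which each covariate is used.

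The cost is analysis wording only, since the variables are already collected. The statistical price is 1 df for the baseline term and more for each extra covariate, with the risk of a smaller or reversed gain shown in step 5.

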### Ethical considerations

The study complies with all the ethical requirements described in the Helsinki Declaration and Resolution 8430, which establishes the norms for health research, according to which this study would be classified as without risk [90]. Responding to these parameters, the researchers built informed consent for the parents and guardians and informed assent for the children. These documents will be signed by all the participants who agree to be part of the study. Additionally, a protocol was established with risk minimization actions. This randomized controlled trial has the endorsement of the Bioethics Committee of the University of Tolima registered in Minutes No. 10 of December 13, 2022.

## Discussion

Proposing a controlled trial protocol to verify the effects of COGNI-MACHINE computational thinking training on executive functions and other cognitive processes of children in the last years of primary school is relevant for the academic community since it will allow knowing the impact of study plans and programs aimed at teaching computational thinking, recognizing the type of activities that have more acceptability, adherence, and effectiveness in children of this age range as well as recognizing the differential impact that the teaching of computational thinking has on different executive cognitive processes.

One of the main strengths of this study will be the blinding of the evaluators to the allocation and the blinding of the investigators in charge of the intervention to evaluate the subjects. On the other hand, the novelty of the COGNI-MACHINE training, compared to other training, is that it seeks to take advantage of different types of activities to promote computational thinking, not only coding activities. This program includes, on the one hand, disconnected activities to introduce students to the development of more complex and abstract activities. On the other hand, it integrates different types of connected activities, starting with animation activities and game programming in the language of blocks, to later develop robotics projects applied to problem-solving.

One of the study's limitations is that, since the application context is school and integrated into the technology curricular program, individual randomization of the participants will not be possible. Therefore, the randomization will be conducted by groups. Additionally, given the nature of the study, participants will not be blinded to the intervention.

## Data Availability

Data will be made available on request. Data will be made available on request.
